## Abstract

**Background:**

The World Federation of Obesity warns that the main health problem of the next decade will be childhood obesity. It is known that factors such as gestational obesity produce profound effects on fetal programming and are strong predictors of overweight and obesity in children. Therefore, establishing healthy eating behaviors during pregnancy is the key to the primary prevention of the intergenerational transmission of obesity. Mobile health (mHealth) programs are potentially more effective than face-to-face interventions, especially during a public health emergency such as the COVID-19 outbreak.

**Objective:**

This study aims to evaluate the effectiveness of an mHealth intervention to reduce excessive weight gain in pregnant women who attend family health care centers.

**Methods:**

The design of the intervention corresponds to a classic randomized clinical trial. The participants are pregnant women in the first trimester of pregnancy who live in urban and semiurban areas. Before starting the intervention, a survey will be applied to identify the barriers and facilitators perceived by pregnant women to adopt healthy eating behaviors. The dietary intake will be estimated in the same way. The intervention will last for 12 weeks and consists of sending messages through a multimedia messaging service with food education, addressing the 3 domains of learning (cognitive, affective, and psychomotor). Descriptive statistics will be used to analyze the demographic, socioeconomic, and obstetric characteristics of the respondents. The analysis strategy follows the intention-to-treat principle. Logistic regression analysis will be used to compare the intervention with routine care on maternal pregnancy outcome and perinatal outcome.

**Results:**

The recruitment of study participants began in May 2022 and will end in May 2023. Results include the effectiveness of the intervention in reducing the incidence of excessive gestational weight gain. We also will examine the maternal-fetal outcome as well as the barriers and facilitators that influence the weight gain of pregnant women.

**Conclusions:**

Data from this effectiveness trial will determine whether mami-educ successfully reduces rates of excessive weight gain during pregnancy. If successful, the findings of this study will generate knowledge to design and implement personalized prevention strategies for gestational obesity that can be included in routine primary care.

**Trial Registration:**

ClinicalTrials.gov NCT05114174; https://clinicaltrials.gov/ct2/show/NCT05114174

**International Registered Report Identifier (IRRID):**

DERR1-10.2196/44456

## Introduction

The World Obesity Federation warns that the main health problem of the next decade will be childhood obesity [1,2]. Obesity and its consequences have their origin in intrauterine life [3]. A study showed that the consumption of “junk” food (high in energy and poor in micronutrients) during pregnancy was a predictor of high birth weight and the child’s future preference for foods high in fat, sugar, and salt [4]. The risk of obesity in childhood is increased if the mother has a high level of adiposity or develops gestational diabetes, or if the baby is not breastfed or experiences poor nutrition that leads to delayed birth [2]. Excessive gestational weight gain (eGWG) is a predictor of overweight and obesity in children in the short-, medium-, and long-term, with evidence of effects up to 21 years after delivery [5-7]. In this sense, according to Barker theory, nutrition and other environmental factors to which the mother is exposed during pregnancy alter intrauterine life [8]. Gestational obesity produces deep effects on the programming of the fetal genome, thereby inducing changes in the prenatal metabolism that extend to the postnatal period, which is also associated with increased susceptibility to developing cardiovascular and metabolic diseases in adulthood [5-7,9,10].

eGWG during early pregnancy has been repeatedly associated with increased adiposity in childhood and adolescence [11-15]. Thus, adequate maternal nutrition during pregnancy is the window of opportunity to strengthen the health status of the mother and fetus and reduce the risk of adverse birth outcomes, such as preterm birth and low birth weight associated with eGWG [16]. The first trimester of pregnancy is critical for short-term interventions to break the “transmission” of obesity from one generation to the next [17]. For many women, pregnancy is a powerful motivator for self-care, as they are more aware of personal risks and have a strong emotional response toward adopting risk-reducing behaviors [18]. Quantitative literature suggests that the key to maintaining a healthy pregnancy and the primary prevention of maternal-fetal complications is establishing healthy dietary behaviors during gestation [19,20]. Even though many women are aware of the importance of healthy eating during pregnancy, the lack of nutritional self-care knowledge represents a substantial barrier to weight control during this stage [21,22]. Nutrition education improves nutritional knowledge, thus influencing practices aimed at achieving adequate nutrition [22]. Several studies recommend the continuous use of educational interventions on nutrition during pregnancy in routine obstetric practice to improve the quality of life of pregnant women and their offspring [6,23-25]. Regarding this, a study performed on the Chilean population evaluated the efficacy of a low-intensity, high-coverage nutritional intervention at the primary health care level [26]. This high-coverage intervention included training health professionals on nutritional recommendations, counseling pregnant women on diet and physical activity, and appropriate referral to primary health care centers’ dieticians. The study found that the intervention reduced gestational weight gain and has the potential for successful scale-up [26].

New strategies to engage the target population are required to maintain nutritional recommendations as a priority in the daily decision-making (top of mind) of pregnant women [27]. Interventions based on behavioral theories provide a greater understanding of the underlying mechanisms that determine health-related behavior change and have the potential to be more effective in promoting adherence to weight gain control [28]. The social cognitive theory [29,30] considers the social dimension of the individual since each individual has a belief system and the capacity for self-motivation and positive behavioral changes [29,31,32]. Therefore, technologies such as mobile phones can be useful to effectively address this problem. Mobile phone ownership is widespread among all sectors of society, regardless of socioeconomic status, which gives us the possibility to introduce the mobile health (mHealth) intervention as an important component of future health care practice [32].

mHealth programs are potentially more effective than face-to-face interventions since they make it possible to cover a larger part of the population; moreover, face-to-face interventions are more labor-intensive, time-consuming, and expensive. Furthermore, they are especially useful during public health emergencies, like the recent COVID-19 pandemic [33]. According to the World Health Organization, mHealth has been defined as “medical and public health practice supported by mobile devices, such as mobile phones, patient monitoring devices, personal digital assistants, and other wireless devices” [34]. Mobile phones are personal, portable, and connected devices [30]. This means that messages can be proactively delivered directly to people, while face-to-face activities or visiting a web page require “going” to look for the information, that is, the self-determined motivation of pregnant women. In this sense, a recent meta-analysis that included 12 randomized controlled trials (RCTs) conducted in an adult population of different ages and conditions demonstrates the efficacy of interventions based on mobile phone apps for weight loss [35]. The combined findings of 10 of the studies included in the meta-analysis showed a substantial reduction in BMI (−0.45 kg/m^2^) and body weight (−1.07 kg) in the intervention group [35]. A recently published RCT that aimed to evaluate the efficacy of a digital health intervention on maternal and perinatal outcomes in pregnant women with obesity who attended the maternal-fetal department of the Hospital-Clinic of Barcelona [31] demonstrates that the digital intervention, which was delivered by the midwife through an app, including advice on gestational weight gain and physical activity, found that gestational weight gain was lower and physical activity increased in obese pregnant women in the intervention group [31]. Hence, we aim to evaluate the effectiveness of an mHealth intervention, based exclusively on mobile phone–delivered messages directed to the cognitive, emotional, and psychomotor behavior, called mami-educ, to reduce excessive weight gain in pregnant women who attend family health care centers in urban and predominantly rural areas (Figure 1). The intervention will last 12 weeks and consists of sending messages through the multimedia messaging system (MMS), with food education addressing the cognitive, affective, and psychomotor domains. According to the literature, the basic factors for adopting a healthy behavior are the perceived susceptibility to the perceived threat of a disease, the perceived consequence, such as severity, the perception of the positive benefits of the action, the perceived barriers to action, and the confidence in the ability to succeed, which is perceived as self-efficacy for action [36]. Thus, the messages that address the cognitive domain of learning are aimed at helping pregnant women understand the benefits of a healthy diet and the harm of a diet rich in fats and sugars during pregnancy, while the affective domain will address the beliefs, barriers, and opportunities to achieve the consumption of healthier foods and contribute to the health of the mother-child binomial. Behavior change is initiated and sustained when people feel that they can execute the desired behavior (ie, self-efficacy) and have a reasonable expectation that the behavior will lead to the desired outcome [37]. In this sense, the psychomotor domain seeks to promote self-efficacy by delivering messages about preparations with adequate nutrition for pregnancy and planning actions to avoid eGWG.

**Figure 1 figure1:**

Schematic diagram of the proposed solution. The solution called "mami-educ" consists of sending cognitive, affective, and psychomotor messages through MMS to pregnant women that assist family health centers in urban and rural areas. MMS: multimedia messaging system.

## Methods

### Study Design and Participants

The design of the intervention corresponds to a classic RCT, a design that allows us to prospectively study pregnant women, in which it is intended to compare the effect of the intervention versus the control condition, to establish a cause-and-effect relationship. This design allows us to reduce the risk of comparability bias. The study will be carried out with pregnant women who control their pregnancy in Family Health Centers (CESFAM) of the Metropolitan Region (the capital city of Chile) and the Aconcagua Valley, Valparaiso Region (88 km to the north of the capital). The CESFAM work under the Comprehensive Health Model with a Family and Community Approach, focusing on prevention and health promotion, and are responsible for basic health care, including home care and health rehabilitation actions. These centers focus on families and communities, give importance to community participation, and work with a primary health team that attends to the whole family in health and sickness throughout the life cycle.

### Control Group

Pregnant women enrolled in the prenatal control program receive routine care at the CESFAM.

### Intervention Group

Pregnant women enrolled in the prenatal control program receive routine care at the CESFAM and messages on nutrition (intervention).

### Inclusion Criteria

Chilean- or Spanish-speaking immigrant pregnant women older than 18 years who receive care at the 6 CESFAM in El Bosque, Metropolitan Region and in Segismundo Iturra CESFAM in San Felipe, Aconcagua Valley, Valparaiso Region; who have gestational ages ≤12 weeks (first trimester); who have a single pregnancy; who declare to have a normal pregnancy at the time of starting the intervention; who agree to be randomized; and who have voluntarily signed the informed consent can participate in this study. The pregnant women who participate in the study must have a mobile device that allows the use of MMS.

### Exclusion Criteria

Exclusion criteria include multiple pregnancies, conditions requiring a special diet, participants with psychiatric illnesses or other prepregnancy pathology, and a history of recurrent miscarriages.

### Sample Size Calculation

The total sample consists of 511 participants, which will be divided into 2 groups. In the El Bosque CESFAM, 280 pregnant women were recruited, with an estimated dropout rate of 30% (based on the pilot study carried out) to guarantee the required sample size of 210 pregnant women with a confidence level of 90% and a 5% error. At Segismundo Iturra CESFAM, 231 pregnant women were recruited, with the same estimated dropout rate, to ensure a sample size of 178 pregnant women with a confidence level of 90% and a 5% error. For the calculation of the sample size, the official records of the DEIS regarding the number of pregnant women between 20 and 44 years of age who were treated for prenatal control in the CESFAM of the El Bosque commune and Segismundo Iturra were considered. The recruitment period will be 6 months.

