### Statistical Analysis

The data analysis plan will be governed by the intention-to-treat principle, as we will include all participants who were randomly assigned after recruitment, assuming that participants who drop out are treatment failures. The effectiveness of the treatment will be measured using the chi-square test (χ^2^), comparing the intervention group with the control group in terms of the percentage of women who are classified as having excessive weight gain at the end of pregnancy. To confirm the effectiveness of the intervention, a significant decrease (*P*<.001) of women with eGWG in the intervened group will be expected. For data analysis, the statistical software GraphPad Instat 3.0b and GraphPad Prism 6.0f (GraphPad Software Inc) will be used. *P*<.001 (determined by a 2-sided test) will be considered statistically significant.

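### At the stated 30% dropout, 280 and 231 women leave about 196 and 162 expected completers, not 210 and 178; the allowances actually built in are 25.0% and 22.9%

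*Protocol article*

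**What the plan says.** All of the relevant figures stand in one paragraph, Sample Size Calculation, in the protocol article.

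- Overall: "The total sample consists of 511 participants, which will be divided into 2 groups".
- El Bosque: "280 pregnant women were recruited, with an estimated dropout rate of 30% (based on the pilot study carried out"), and the purpose is "to guarantee the required sample size of 210 pregnant women with a confidence level of 90% and a 5% error".
- Segismundo Iturra: "231 pregnant women were recruited, with the same estimated dropout rate, to ensure a sample size of 178 pregnant women", again at 90% confidence and 5% error.

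The stronger verb, guarantee, is attached only to the 210; the 178 is said to be ensured. The basis given for the two site sizes is official counts of pregnant women in prenatal care, which the article does not print.

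The Statistical Analysis section bears on what dropout does. It adopts intention to treat, keeps everyone randomised, and proceeds by "assuming that participants who drop out are treatment failures".

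**The concern.** A recruitment number, a dropout rate and a post-dropout number are tied together by one line of arithmetic. Here the three disagree at both sites. The article calls 210 a required size and says that recruitment secures it, yet its own pilot-based dropout rate says otherwise. The two sites also imply different dropout allowances, although the text says the rate is the same.

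At stake is whether a reader can tell which dropout rate the trial was planned on (30%, 25% or 23%) and how many women are expected to reach the end of follow-up. Anyone who later compares actual retention with the plan would be using a wrong benchmark.

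**Working it through.** **Inputs** (all from Sample Size Calculation): recruitment N = 280 and 231; dropout d = 0.30 at both sites; post-dropout size n = 210 and 178; total 511. The total is consistent: 280 + 231 = 511.

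**1. Can the recruitment numbers be reproduced?** The correct inflation is N = n / (1 − d).

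- El Bosque: 210 / 0.70 = 300; the article has 280.
- Segismundo Iturra: 178 / 0.70 = 254.3, rounded up to 255; the article has 231.
- Total: 300 + 255 = 555 against 511, a difference of 44.

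Neither number is reproduced.

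**2. What do the recruitment numbers deliver at 30%?** Expected completers = N × (1 − d).

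| Site | N | N × 0.70 | Stated n | Shortfall |
|---|---|---|---|---|
| El Bosque | 280 | 196 | 210 | 14 |
| Segismundo Iturra | 231 | 161.7 | 178 | 16.3 |
| Total | 511 | 357.7 | 388 | 30.3 |

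30.3 / 388 = 7.8%, or about 8%.

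**3. What dropout do the printed pairs allow for?** Implied d = 1 − n / N.

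- El Bosque: 1 − 210/280 = 25.0%.
- Segismundo Iturra: 1 − 178/231 = 22.9%.

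**4. Does one rule explain both pairs?**

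- Multiplying up by 1 + d: 178 × 1.30 = 231.4, which fits 231; but 210 × 1.30 = 273, not 280.
- Dividing by 0.75 (25% dropout): 210 / 0.75 = 280, which fits; but 178 / 0.75 = 237.3, rounded up to 238, not 231.

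No single rate or rule gives both pairs exactly.

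**5. How much precision per site is involved?** The counts behind 210 and 178 are not given, so this step is an assumption: a finite-population formula for a proportion with p = 0.5, 90% confidence (z = 1.645) and a 5% margin. Sizes of 210 and 178 then imply populations M of about 935 and 518. With c completers the margin is z × √[(0.25 / c) × (M − c) / (M − 1)]. With c = 196 it is about 5.2%, and with c = 161.7 about 5.4%, instead of 5.0%.

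**6. What does dropout do to the primary comparison?** Suppose dropout is d in both arms, every dropout is counted as having excessive gain, and the completers' proportions are p₁ and p₂. The analysed proportions are d + (1 − d)p₁ and d + (1 − d)p₂, so their difference is (1 − d)(p₁ − p₂). The completers' difference is multiplied by 0.70 at 30% dropout, against 0.75 and 0.77 at 25.0% and 22.9%. The denominator is unchanged.

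**The case against.** The arithmetic itself has no good defence: the figures are in intact prose, gaps of 14 and 16 women are not rounding, and nothing elsewhere in the article repairs them. The case on the other side is about how much follows. A reader might infer four stronger things, and the document supports none of them.

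- **That only about 358 women will be analysed.** The primary chi-square test takes all randomised women, with dropouts as failures. Its denominator is 511 if the target is met. Calling the completers evaluable, or quoting power for 358, would set Sample Size Calculation against Statistical Analysis.
- **That the shortfall costs power.** The article derives 210 and 178 from a confidence level, an error margin and population counts, with no effect size, control rate or power. The 388 is therefore not shown to be a requirement for comparing two arms, and missing it by 8% demonstrates no loss of power. On the assumption in step 5 the loss of precision is slight.
- **That the trial must enrol 555.** That is only the correct inflation of 388. It does not make the trial adequately sized for its comparison.
- **That the sites used two identifiable wrong formulas.** That 280 came from 210/0.75 and 231 from 178 × 1.30 is inference from numbers that happen to fit. The article does not show its method; only the implied allowances are established.

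It can also be said that accrual matters more. The Results section reports 76 women who had agreed and answered the survey by 30 November 2022, after a start on 2 May 2022, so a gap of 44 in a recruitment target is unlikely to be what limits the trial.

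All of this stands as a limit on the consequence. None of it makes the printed dropout statement true, and step 6 shows that the dropout rate still bears on the primary comparison.

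**Conclusion.** The point holds as an arithmetic inconsistency in the stated sample size. At 30% dropout the plan yields 196 and about 162 expected completers, about 358 in total, against 210, 178 and 388: some 30 women, or 8%, short. The allowances actually built in are 25.0% and 22.9%, neither of them the stated rate and not equal to each other. This rests only on printed figures.

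The consequence is modest. The number analysed under intention to treat is unaffected; the higher dropout rate shows up as more dilution of the arm difference. The dilution factors assume equal dropout in both arms, and the precision figures assume p = 0.5 and a finite-population formula. The sentence should be corrected, but it does not by itself call for more recruitment.

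**What to change.** Restate the paragraph in one of two ways, leaving enrolment at 511.

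1. Keep the pilot-based 30% and report what it gives: 511 randomised women, about 358 expected completers (196 at El Bosque and 162 at Segismundo Iturra). Restate any per-site precision claimed for completers to match.
2. Keep 210 and 178 and state the dropout actually allowed for, 25% and 23%. This departs from the pilot figure that the article cites, so it needs a reason.

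If 388 completers is to remain the target at 30% dropout, the recruitment number must read 555 (300 + 255); that is the only version that changes enrolment.

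In any version, use the term expected completers rather than evaluable, and add that the primary intention-to-treat analysis includes all randomised women with dropouts counted as failures, so that dropout dilutes the comparison and does not reduce the analysed number.

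Either of the two restatements costs a corrected sentence. The only loss is a less favourable expected number of completers or a less conservative stated dropout rate.

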### Randomization and Masking

The pregnant women who meet the inclusion criteria are invited to participate in the study, as are those who accept and sign the informed consent form. These pregnant women receive the link to the diagnostic survey on their telephones and are then randomized to be included in the intervention. At the end of each month of the recruitment period, the researchers will randomize the pregnant women who were recruited during that month. A stratified randomization will be carried out to ensure a sample that is as balanced as possible. The sample will be divided into 4 strata according to their pregestational weight, classifying them as underweight (BMI<18.5 kg/m^2^), normal weight (BMI 18.5-24.9 kg/m^2^), overweight (25-29.9 kg/m^2^), and obese (BMI≥30 kg/m^2^). Simple random selection will be carried out then by generating a table of random numbers without repetition, from 1 to n, and deciding a priori that it will be read from left to right, with even numbers assigned to the control group and odd numbers to the intervention group.

A single-blind study will be carried out since the CESFAM personnel who will oversee the recruitment will be blinded to the randomization of the subjects to avoid bias in routine care.

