## Results

The study was funded by the National Research and Development Agency of Chile in December 2021. The data collection began on May 2, 2022. Study staff have been engaged in activities associated with study including enrollment and data collection. As of November 30, 2022, a total of 222 pregnant women have been admitted for the first prenatal appointment, 127 meet the inclusion criteria, and 76 agree to participate and answered the diagnostic survey. The expected timeframe for completing recruitment and data analysis is November 2023.

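### The fixed odd-number rule gives the surplus woman of every odd-sized monthly BMI batch to the intervention and assigns a lone woman with certainty; the effect is real but modest

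*Protocol article*

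**What the plan says.** The protocol article, under Randomization and Masking, sets out the allocation procedure in sequence:

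- Timing: "At the end of each month of the recruitment period, the researchers will randomize the pregnant women who were recruited during that month".
- Aim: "A stratified randomization will be carried out to ensure a sample that is as balanced as possible".
- Strata: "The sample will be divided into 4 strata according to their pregestational weight" (underweight, normal weight, overweight, obese). Commune is not named as a stratum.
- Draw: "Simple random selection will be carried out then", by "generating a table of random numbers without repetition, from 1 to n".
- Rule: "with even numbers assigned to the control group and odd numbers to the intervention group".

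The parity rule is fixed in advance, and no step alternates or randomises it. The symbol n is not defined. No numerical allocation ratio is given. Sample Size Calculation says only: "The total sample consists of 511 participants, which will be divided into 2 groups". On progress to 30 November 2022, Results reports that "127 meet the inclusion criteria, and 76 agree to participate and answered the diagnostic survey".

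**The concern.** The integers 1 to n contain one more odd than even number whenever n is odd. If the numbering restarts in each stratum each month, the extra woman in an odd-sized batch can only go to the intervention. Such surpluses add up rather than cancel. When a batch holds one woman, the only number is 1, so her arm is known before the draw.

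Three things are at stake. The overall ratio drifts above 1:1. The chance of intervention depends on batch size and therefore on BMI stratum, with the largest departure in the rarest stratum. And the primary test under Statistical Analysis is an unadjusted chi-square on excessive gestational weight gain, which does not correct for a BMI difference that the allocation rule itself creates.

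**Working it through.** **Inputs from the protocol article.** Monthly batches, four BMI strata, odd = intervention (Randomization and Masking). 76 women from 2 May to 30 November 2022, about 7 months (Results). Target 511 (Sample Size Calculation). Recruitment of 6 months (Sample Size Calculation, Procedures) or May 2022 to May 2023, about 12 months (Abstract, Results). There is no stated ratio to reproduce.

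**Assumption.** The BMI mix is not given. Three mixes (underweight/normal/overweight/obese, %) were used: 3/35/34/28, 5/45/30/20 and 2/30/35/33.

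**Step 1: one batch.** A permutation of 1..n has ceil(n/2) odd and floor(n/2) even numbers.

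| n | Intervention : control | Chance of intervention |
|---|---|---|
| 1 | 1 : 0 | 1.00 |
| 2 | 1 : 1 | 0.50 |
| 3 | 2 : 1 | 0.667 |
| 4 | 2 : 2 | 0.50 |
| 5 | 3 : 2 | 0.60 |
| 7 | 4 : 3 | 0.571 |

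The chance is never below 0.50.

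**Step 2: batch size.** 76/7 = 10.9 women per month, and 10.9/4 = 2.7 per stratum-month. At the planned pace, 511/(6×4) = 21.3; over 12 months, 511/(12×4) = 10.6.

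**Step 3: accumulated surplus.** For N women over M months and a stratum with share q, let p = q/M. Then P(odd batch) = [1 − (1 − 2p)^N]/2. Expected surplus = M × the sum of P(odd) over strata, and expected intervention count = (N + surplus)/2. Example, first mix, N = 76, M = 7: P(odd) is 0.24 for underweight and about 0.50 in each other stratum. The surplus is 7 × 1.74 = 12.2, so the split is (76 + 12.2)/2 = 44.1 vs 31.9. Expected lone women = M × sum of N·p·(1 − p)^(N−1).

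| Scenario | Surplus | Intervention vs control | Lone women (share) | Underweight women going to intervention |
|---|---|---|---|---|
| 76 in 7 months | 11.7–12.8 | 43.9–44.4 vs 31.6–32.1 | 3.3–5.0 (4.4–6.6%) | 81–91% |
| 511 in 6 months | 11.9–12.0 | 261.5 vs 249.5 | 0.4–1.9 (0.1–0.4%) | 56–64% |
| 511 in 12 months | 22.9–23.9 | 267.0–267.5 vs 243.5–244.0 | 3.1–4.4 (0.6–0.9%) | 62–74% |

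**Step 4: efficiency.** With intervention share s, efficiency relative to 1:1 is 4s(1 − s): 4 × 0.58 × 0.42 = 0.974 for 76 women, 0.998 at 52.3% and 0.999 at 51.2%.

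**Step 5: bias in the crude comparison.** With no true effect, the expected crude difference is the sum over strata of (stratum share of intervention arm − stratum share of control arm) × stratum risk. First mix, 76 women: 0.03 × 76 = 2.28 underweight women split 1.98 vs 0.30, that is 1.98/44.1 = 4.5% vs 0.30/31.9 = 0.9% of the arms. The documents give no risks by stratum. Four assumed risk sets were tried, rising from 10–20% (underweight) through 30–40% and 50–60% to 60–70% (obese). The difference favours the intervention by:

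- 511 in 6 months: 0.1 to 0.5 percentage points (standard error about 4.4)
- 511 in 12 months: 0.2 to 0.8 points (standard error about 4.4)
- 76 women: 0.2 to 1.4 points (standard error about 11.6)

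**Step 6: other readings of n.** If n is the whole month's intake, the surplus is at most one woman per month (6, 7 or 12 in all). A woman alone in her stratum then has a chance of 6/11 = 0.545 at n = 11 and 43/85 = 0.506 at n = 85. The BMI strata, however, no longer constrain the allocation. If the table runs well beyond the batch size, the draw is close to simple randomisation and again does not enforce balance.

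**The case against.** The best defence is that n is undefined. The order of the sentences favours the stratum-month reading but does not settle it, and an article may condense a fuller procedure. This stands as a limit: the drift and the certain allocations follow only on that reading. It does not clear the text, because under the other two readings the stated stratification is not enforced.

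Four stronger inferences are tempting, and the documents do not support them.

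- That the rule fails to balance the strata. Within a batch, a split differing by at most one is the tightest possible. The fault is only that the surplus always falls the same way.
- That underweight women would have almost no controls. The 81–91% figure belongs to the 76-woman snapshot, where that stratum holds about 1.5 to 4 women under the assumed mixes. At 511 women, 26–44% of underweight women would be controls. Moreover, the 76 are women who agreed and answered the survey, not a stated randomised count.
- That BMI confounding undermines the primary test. Step 5 puts the bias well below sampling error.
- That recruiters could exploit certain allocations. Randomisation takes place at month end, after consent, and the recruiting staff are blinded to it, so the scope is small.

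**Conclusion.** The defect holds on the natural reading of the text. The parity rule is exact in its effect: a surplus of one for the intervention in every odd-sized stratum-month, none in even-sized ones, and certain allocation at n = 1. Its size depends on the pace of accrual and on an assumed BMI mix. It amounts to roughly 58:42 at the pace reported to November 2022, and 51:49 to 52:48 if 511 women are recruited over 6 to 12 months. The loss of efficiency is about 3% at most. Under the assumed risks, the bias in the crude comparison is below 1 percentage point at the planned size and about 1 point for 76 women. It should be corrected because it is avoidable, runs in one direction and leaves some women unrandomised. It does not by itself threaten the trial's conclusion.

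**What to change.** For the remaining intake:

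1. Define n as the number of women in one BMI stratum in one monthly batch.
2. In each stratum-month, decide by a random draw with probability 1/2 whether odd or even means intervention. Every woman's chance is then 0.50 for any n, including n = 1, and the expected surplus is zero. Alternatively, prepare one permuted-block list per BMI stratum in advance and carry it over from month to month. If commune is made a stratum, apply the same method there, since the batches become smaller still.
3. Women already randomised keep their allocation.
4. Add a BMI-stratified analysis of the primary outcome, for example Mantel-Haenszel.

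The allocation change costs little more than a revised script or list. The stratified analysis has a small cost of its own: it departs from the unadjusted chi-square under Statistical Analysis, so it should be documented as an amendment, with its date and reason, before outcomes are compared by arm.
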